## **5.3 Treatment**

Based on the result of the randomisation, patients are allocated to one of the two treatment arms. The study intervention (IPT) and the control arm are described in detail below.

### **5.3.1 General procedures in both study arms**

Before the start of the group, in both study arms one individual preliminary talk of app. 30 minutes will be conducted in which an interpersonal inventory is performed and the indication of involvement of the employer and/or a social worker is determined (no documentation in eCRF required).

To check for adherence and to support the supervision, a ‘Therapeutic Element Checklist’ (Stundenbogen) for IPT-Work (e.g. strategies for addressing work-life-balance, demand-control-balance, effort-reward-balance, and work as a social role) and SP (e.g. reflective listening,

facilitation of affect, helping the patient to feel understood) is filled out by the therapist immediately after each group session.

No additional psychotherapeutic treatment is allowed throughout the study including the follow-up visit.

Antidepressive medication is allowed if stable for at least 4 weeks before randomisation and throughout the follow-up period. The continuous intake of benzodiazepine is prohibited; the selective use of benzodiazepine as rescue medication on-demand for a maximum of 2 weeks is permitted. Other required medication for comorbid somatic diseases will be allowed and documented.

During group sessions, study psychotherapists will encourage patients to report any adverse events either during the session or confidentially. The psychotherapist will document adverse events as described in section 7.

### **5.3.2 IPT-Work (intervention arm)**

The IPT-Work condition follows a manual and focuses on the work context by adding specific elements to the regular IPT strategies in four modules of

1. work-life-balance: identifying work-related stress factors and allostatic overload; psychoeducation on the association of work stress, social support and depression; creating a balance between performance values and interpersonal values; teaching mindfulness skills (as a different therapeutic intervention) to reduce physical and mental tension/stress,
2. demand-control-balance: enhancing communication skills at work (e.g. negotiating modified work tasks or working hours) to cope with difficult work situations; set limits to exaggerated demands (prevent allostatic overload; get a sense of control over the work conditions e.g. organisational injustice); ask for support; cope with interpersonal conflicts and difficult role transitions at the workplace,
3. effort-reward-balance: identify values at work; set self-exertion and reward in balance,
4. work as a “social role”: define your work place with strengths and limitations. The intervention includes 10 group sessions (twice weekly in the first 2 weeks, 1 weekly thereafter) of 90 minutes for 4-6 outpatients over 8 weeks.

### **5.3.3 Supportive Psychotherapy (SP, control arm)**

SP is a manual-based, nonspecific, non-work-directed psychotherapeutic intervention found to be effective in the treatment of depression. SP will be applied in the same format (group sessions), frequency, intensity, and duration as the IPT-Work condition in order to implement a homogeneous and comparable control group. It resembles supportive clinical management or client-centred counseling and includes psychoeducational elements and other common aspects of psychotherapy, such as reflective listening, facilitation of affect, helping the patient to feel understood, empathy, hope, and therapeutic optimism. Specific interpersonal, cognitive, behavioral, and psychodynamic interventions were explicitly proscribed. Since SP is based on exclusively common therapy effects (common factors approach) and IPT-Work elicits common as well as specific therapy effects, using SP as control group enables an estimate of the specific effects of IPT-Work beyond the common therapy effects.

## **5.4 Follow-up evaluations**

### **5.4.1 Blinding of raters**

At the beginning of each interview, patients are reminded that the raters are blinded. They are therefore asked to refrain from making any references in the interview that would allow the rater to draw conclusions about the study arm that the patient has been assigned to.

If a rater for any reason is unintentionally unblinded, this does not constitute a reason for the patient to be excluded from the study. Depending on the personnel resources of the local study team, the unblinded rater should be replaced by another, blinded rater. If this is not possible, data that is collected unblinded must be labelled as such.

### **5.4.2 Post-treatment, Follow-up / End of Trial**

After end of treatment, patients will participate in two subsequent evaluations at post-treatment ( $W9 \pm 7$  days) and follow-up ( $W21 \pm 7$  days) to assess their condition after study psychotherapy. All evaluations will be conducted by the respective trained and blinded raters (preferably the same person who was responsible for the study inclusion) according to the details described above.

## **6 Discontinuation criteria**

### **6.1 Premature termination of one of the treatment arms or the entire study**

The coordinating investigator is under obligation to monitor the progress of the study with regard to safety-relevant developments and, if necessary, initiate the premature termination of a treatment arm or the entire study. The coordinating investigator will be supported in this responsibility by the DSMB, if necessary.

A study arm or the entire study must be terminated prematurely if:

- the benefit-to-risk ratio for the patients changes markedly,
- the coordinating investigator or the DSMB considers that the termination of the study is necessary,
- indications arise that the study patients' safety is no longer guaranteed,
- the question(s) addressed in the study can be clearly answered on the basis of results of another study on the same subjects,
- an insufficient recruitment rate makes a successful conclusion of the study unrealisable or no longer feasible.

If the study is prematurely terminated or suspended for any reason, the investigator should promptly inform the study patients and ensure appropriate therapy and follow-up for the patients. Where required by the applicable regulatory requirements, the IEC(s) will also be informed (this is usually done by the coordinating investigator).

### **6.2 Premature termination of the study at one of the sites**

The investigator or coordinating investigator has the right to terminate the study at one of the sites.

The study can be terminated prematurely at a site by the investigator if, for instance unforeseeable circumstances have arisen at the site which preclude the continuation of the study, the investigator considers that the resources for continuation are no longer available, the investigator considers that the continuation of the study is no longer ethically or medically/psychologically justifiable.

The coordinating investigator can initiate the exclusion of a site from further participation if, for instance, patient recruitment is inadequate, serious problems arise with regard to the quality of the collected data which cannot be resolved.

Premature termination at one of the sites does not automatically mean a termination of the study for already enrolled patients. A separate decision on further treatment must be made for each patient, depending on the overall situation. Adequate further treatment and follow-up of already enrolled patients must be ensured. The documentation of already enrolled patients will be reviewed for completeness and plausibility. Queries may be raised for further clarification before the site is closed. These queries must be answered properly by the site. The IEC(s) must be duly notified of the site's closure, including reasons, within the specified period. The study site concerned will be closed in stages by the CRA when a decision has been made on the further treatment of the patients concerned.

### **6.3 Discontinuation of study treatment or study participation for individual patients**

It has to be distinguished if study treatment of a patient has been stopped prematurely or if the study participation of a patient was stopped prematurely.

In the case study treatment of a patient has been stopped prematurely, further follow-up visits and the assessment of the study endpoints are essential to enable an analysis of the full analysis set according to the intention-to-treat principle. Further visits, follow-up and documentation should always be striven for / ensured in this case. This includes the follow-up of AEs, the time of termination, the results available at that time and, if known, the documentation of the termination of treatment on the eCRF and in the medical/psychological record, giving reasons, a final examination and documentation according to the protocol (if possible).

In the case study participation of a patient was stopped prematurely, the conduct of further follow-up visits is no longer possible. The documentation should be completed as far as possible under these circumstances, e.g. a final examination and documentation according to the protocol (if possible), a documentation of the premature study termination on the eCRF and in the medical record, giving reasons, appropriate further treatment and follow-up outside the study should be ensured.

A study patient can withdraw his/her consent at any time, without having to give reasons, and have his/her entire study participation terminated prematurely. However, the prerequisite for this is that the patient actively terminates study participation by withdrawing his/her consent for the follow-up and documentation.

The responsible investigator may only withdraw a patient from participation in the study in case of extreme circumstances arise which make any study-relevant follow-up impossible.

## **7 Safety monitoring and documentation**

### **7.1 Definition of adverse events (AEs) and serious adverse events (SAEs)**

An AE in this study is defined as any untoward medical occurrence in a patient who has been randomised.

The following adverse events (AEs) will be documented to monitor safety of randomised patients according to one of the following categories (select main category)

- A) Worsening of psychopathological symptoms
- B) Appearance of new psychopathological symptoms

- C) Passive suicidal thoughts
- D) Active suicidal thoughts
- E) AEs related to the patient–therapist relationship
- F) AEs related to personal life
- G) AEs related to occupational life
- H) Other (i.e., non-psychopathological) AEs (e.g. influenza or fractures)

A serious AE (SAE) in this study is defined as any untoward medical occurrence that results in any of the following outcomes:

- Death
- Life-threatening situation (patient is at immediate risk of death)
- Inpatient hospitalisation or prolongation of existing hospitalisation (pre-planned hospitalisations do not have to be considered)
- Persistent or significant disability/incapacity
- Failed suicide attempt
- Other important medical event: An event that does not fit any of the other outcomes above, but may jeopardise the patient and may require medical or surgical intervention (treatment) to prevent one of the other outcomes above.

These definitions are based on a standardised questionnaire already applied in previous psychotherapy trials.

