## 7.2 Documentation of AEs and serious AEs (SAEs)

(Serious) adverse events have to be documented in the eCRF beginning from the date of randomisation and ending with the date of the study end.

The documentation obligation of AEs applies to the study psychotherapist or rater who first became aware of the event.

- Characterisation of the event (see above listed events, in case of “Other AEs”, a diagnosis/symptoms have to be provided, symptoms only if diagnosis not yet available)
- Onset/end date
- Severity (mild to severe)
- Relationship to study procedure
- Serious / non-serious (yes/no; yes, if one of the SAE criteria is met)
- Outcome

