### 10.5.9 Analysis of safety

Adverse events are described by main categories A-H (see section 7.1). The incidences of adverse events will be summarised in the SAF by treatment arm with two-sided 95% confidence intervals based on Wilson scores (without continuity correction) according to method 3 in Newcombe (1998).

The AEs will be displayed in summary tables by treatment as follows:

The total number of AEs, the minimum, maximum and mean number of AEs per patient will be calculated per main category A-H and in total.

The incidence of AEs defined by main categories A-H will be calculated as the number of patients who experienced at least one AE with the respective category A-H in percentage of the total number of patients.

Each table will be produced for the following AE-sets:

- All AEs
- All Serious Adverse Events (SAEs)

Additionally, these tables will be recalculated for AEs with onset during the treatment period and for AEs with onset after the treatment period.

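### The fixed adverse event list A–H defines no category for suicidal behaviour or self-injury, and no safety table in the protocol shows such events separately by arm

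*Protocol*

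**What the plan says.** Section 7.1 sets a broad definition: "An AE in this study is defined as any untoward medical occurrence in a patient who has been randomised". Suicidal behaviour and self-injury after randomisation fall within it.

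Events are then documented "according to one of the following categories (select main category"). Two of the eight categories concern suicidality, "C) Passive suicidal thoughts" and "D) Active suicidal thoughts". A and B cover worsening and new psychopathological symptoms; E, F and G cover the therapeutic relationship, personal life and occupational life. The residual category is "H) Other (i.e., non-psychopathological) AEs (e.g. influenza or fractures").

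The SAE definition in the same section lists death and, separately, "Failed suicide attempt".

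Section 7.2 lists what is recorded for each event. A specific description is required for the residual category only; there, "a diagnosis/symptoms have to be provided, symptoms only if diagnosis not yet available". Seriousness is listed as a yes/no item. Section 7.3 adds an SAE form, whose content is not in the protocol. Section 8.4 names no AE coding other than the section 7.1 categories.

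Section 10.5.9 opens with "Adverse events are described by main categories A-H (see section 7.1"). Event counts are given per category and in total, patient incidence by category, and each table is made for all AEs and for all SAEs by treatment. The synopsis plans overall AE and SAE incidence by arm with confidence intervals, and Table 3 (section 2.4) names a risk difference.

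**The concern.** The list separates two grades of suicidal thought but has no category for suicidal acts, and the wording of the residual category excludes events of a psychopathological nature. The authors foresaw a suicide attempt, since it is a seriousness criterion, yet the person recording one is not told which category applies. Section 7.2 gives the task to whichever therapist or rater first learns of the event, and six centres take part, so nothing in the text ensures uniform filing. Therapists also know the treatment arm (section 3.4), so discretionary filing is done partly by unblinded staff.

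Table 1 sets a comparative safety objective, and suicidality has its own section (7.4). A reader of the trial report would expect to see how many patients in each arm showed suicidal behaviour or self-injury. The tables the protocol specifies do not answer that.

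**Working it through.** The protocol gives no figure on this point, so there is nothing to recompute. The check follows three kinds of event through sections 7.1, 7.2, 7.3 and 10.5.9.

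| Event | Seriousness criterion met (7.1) | Counted in totals by arm | Category row (7.1, 10.5.9) | Record that would identify it later (7.2, 7.3) |
|---|---|---|---|---|
| Completed suicide | Death | AE and SAE totals | None defined | SAE form (content not shown) |
| Failed suicide attempt | Named criterion | AE and SAE totals | None defined | SAE form (content not shown) |
| Self-injury meeting no seriousness criterion | None | AE total only | None defined | Required description only if filed under H |

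**Where such an event could go.**
- C and D name thoughts. An act could be placed in D by extension, but the label does not say so.
- A and B are broad enough to receive it as a worsened or new symptom.
- H could receive it only against its own wording.

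A, B, D and H are thus the likely receiving categories.

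**What the tables then show.** In the row for A, B, D or H the event is mixed with worsened symptoms, new symptoms, suicidal thoughts or somatic events respectively. In the SAE tables a suicide or attempt is mixed with the other SAEs of that category and in total. No table is specified by seriousness criterion or for suicidal behaviour.

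**What can be recovered.** For a suicide or an attempt, recovery depends on what the SAE form records. For non-serious self-injury under H, the required diagnosis or symptoms should identify it. Under A, B or D, section 7.2 requires only dates, severity, relationship, seriousness and outcome besides the category, and none of these distinguishes self-injury from another symptom. That loss arises at data capture, so a later table cannot repair it.

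**The case against.** Several points on the other side are sound.

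- The instruction asks for a main category, which is a best fit, and A, B and D can each receive such an event. It would be wrong to say that these events have no place at all; what is missing is a defined one. That sites would file differently is a reasonable expectation, not something the document shows.
- A reader might infer that suicidal behaviour cannot be counted by arm, or that every safety table rests on A–H alone. The text does not support either. Totals are planned beside the category rows, all tables are repeated for SAEs, and a suicide or failed attempt enters the SAE total of its arm whatever category is chosen. An SAE form is also completed, and the DSMB is informed of observed adverse events (section 11).
- A reader might express the loss as one attempt among about 72 patients in an arm turning into none. That comparison needs a suicide-attempt row, and none is planned. In the SAE total, filing under a different category changes nothing.
- A reader might also infer that C and D mix unchanged baseline thoughts with new ones, because they lack the conditions of worsening or newness in A and B. Section 7.2 starts documentation at randomisation and asks for an onset date, and section 7.4 directs staff to assess change of status at every visit, so this is weak. Nor could HRSD-24 and BDI-II item scores decide the question during treatment: Table 5 schedules those scales at V0, V12 and V13, whereas AEs are recorded from V2 onwards.
- Section 7.1 bases its definitions on a questionnaire used in earlier psychotherapy trials. Keeping an established instrument is defensible, and its coding guidance is not visible here. Prior use does not, however, supply the missing category.
- The analysis plan is not shown and may add tables, including SAEs by seriousness criterion. It cannot add a distinction that was not captured.
- Section 8.2.1 has adverse events noted in the medical record, which may hold more detail. That would help source review, but it is not a database field from which tables are built.

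**Conclusion.** The point holds in limited form. The category list, which the protocol fixes, has no defined category for suicidal behaviour or self-injury. Suicides and failed attempts are counted in the totals by arm but are not reported separately in any protocol-specified table. Self-injury that meets no seriousness criterion is the real gap: it enters the AE total only, in an undefined category, and without a required description unless it is filed under H.

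No numerical size applies, because the protocol gives no expected event rate and plans no table in which a misfiled event would alter a suicidal-behaviour count. Safety is evaluated descriptively (section 2.2.2), and no confirmatory result depends on A–H. This is therefore a cheap improvement to safety reporting, not a threat to the trial's main conclusion.

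The conclusion assumes that the eCRF follows section 7.2 as written and that no guidance outside the protocol already directs such events to one category. If the SAE form records the criterion met, serious events can be identified later; non-serious self-injury under A, B or D still could not be identified from the AE items that section 7.2 requires.

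**What to change.** Add one main category to section 7.1 and the eCRF list, for example: suicidal behaviour / self-injury (completed suicide, attempt, self-injury). Extend section 10.5.9 so that this category is reported by arm in the AE and SAE tables like the others. Recode events already entered where a description or an SAE form allows, preferably without knowledge of the arm, and state how many could not be checked. The change concerns data capture and reporting only; clinical management is untouched.

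A table of SAEs by seriousness criterion and arm would be a useful addition but is optional and belongs in the analysis plan.

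The cost is a minor amendment, one further value in the eCRF list, a small departure from the earlier questionnaire, and recoding of what should be few events. Acting early matters, because events recorded without a description cannot be sorted afterwards.

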## 7.2 Documentation of AEs and serious AEs (SAEs)

(Serious) adverse events have to be documented in the eCRF beginning from the date of randomisation and ending with the date of the study end.

The documentation obligation of AEs applies to the study psychotherapist or rater who first became aware of the event.

- Characterisation of the event (see above listed events, in case of “Other AEs”, a diagnosis/symptoms have to be provided, symptoms only if diagnosis not yet available)
- Onset/end date
- Severity (mild to severe)
- Relationship to study procedure
- Serious / non-serious (yes/no; yes, if one of the SAE criteria is met)
- Outcome

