- Return to Work Attitude (RTW-SE): is a self-rated questionnaire to assess return-to-work self-efficacy for employees with mental health problems. Higher scores correspond to higher self-rated return-to-work self-efficacy.
- Effort-Reward-Imbalance (ERI): The ERI is a self-rated questionnaire to assess imbalances between work-related efforts and rewards. Higher scores correspond to a higher effort-reward-imbalance. There are three subscales assessing effort (ERI1-ERI6), reward (ERI7-ERI16) and over-commitment (OC1-OC6).
- Job Content Questionnaire 2 (JCQ2): The JCQ2 is a self-rated questionnaire designed to measure the "content" of a respondent's work tasks in a general manner which is applicable to all jobs and jobholders. The JCQ2 covers critical workplace issues that are often overlooked - because they are very difficult to assess - including employee health risks, chronic disease, depression, sickness-absence, disability - and also job satisfaction, active work/creativity, and innovation potential. It is used to measure the high-demand/low-control/low-support model of job strain development and predicts stress-related risk and active-passive behavioral correlates of jobs according to the demand/control model. Higher scores correspond to higher job strain.
- Quality of Life (WHOQOL-BREF): The WHO Quality of Life Instrument (WHOQOL-BREF) is a short form tool consisting of 26 items divided into four domains (physical health, psychological health, social relationships and the environment) to measure quality of life. Higher scores correspond to higher domain-specific quality of life.
- Connor-Davidson Resilience Scale (CD-RISC): The CD-RISC is a self-rated questionnaire to assess resilience. Higher scores correspond to greater resilience.

In addition, exploratory endpoints include

- Number of self-reported days of sick leave throughout the study period.

Safety is assessed in terms of rates of AEs and SAEs.

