### **3.4 Methods against bias**

For logistical reasons, clusters of 4-6 eligible patients at a time will be randomised to group psychotherapy according to the IPT-Work or SP condition. To avoid selection bias, the raters who identify eligible patients and obtain informed consent will not be informed about the randomisation result, nor about ongoing or previous IPT-Work or SP psychotherapy groups at their respective centre.

To further avoid selection bias, the randomisation code to allocate patient groups to interventions will be generated by the CTU using the following procedure to ensure that treatment assignment is unbiased and concealed from patients and site staff. Randomisation of patient groups will be performed, stratified by centre, in blocks of variable length with a 1:1 ratio. The block lengths will be documented separately and will not be disclosed to the centres. The randomisation code will be produced by validated programmes based on the Statistical Analysis System (SAS).

Obviously, blinding of patients and study psychotherapists performing the interventions is not possible. However, data acquisition other than patient reported outcomes will be done by trained blinded clinical raters not involved in patient management. Each site will implement procedures to mask patient treatment assignment from the clinical rater by reminding the patients at each visit not to mention anything that might reveal their treatment condition. Diagnostic training of raters in the SCID-5, HRSD-24 and (S)AE assessments will be conducted by expert trainers and interrater reliability will be ensured. The other measures are self-rated in a standardised questionnaire format.

All confirmatory analyses are fully specified in the trial protocol to avoid reporting bias. The trial is registered prospectively at the German Clinical Trials Register (see chapter 13), and its results will be published irrespective of the outcome to prevent publication bias.

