## 10.4 Sample size calculation

In the pilot trial, mean $\pm$ SD relative changes (decreases) from baseline to follow-up of HRSD-24 were 62.2% $\pm$ 28.0% and 22.6% $\pm$ 71.6% for IPT-Work and TAU, respectively, data not shown). On the basis of a two-group t-test at two-sided significance level of 5%, a sample size of 62 observations per arm yields a power of 80% to detect a difference if the HRSD-24 mean relative changes from baseline at follow-up are assumed to differ by 28.0% points with a common SD of 55.0% (nQuery Version 9.2.0.0). The common SD is estimated to lie in between SDs seen in the pilot trial for IPT-Work and TAU, since IPT-Work and SP have similar treatment intensity. The means difference is considered both minimum clinically relevant and realistic since IPT is generally more effective than SP and IPT-Work is specifically tailored to depression in a work context. This calculation is conservative given that evaluation in a linear model adjusting for baseline measurement will further increase the power. Due to IPT-Work and SP group sizes (clusters) of only 4-6 participants and the fact that the interventions are directed at patients, the design effect induced by intracluster correlation is conservatively estimated as 1.04, yielding an increase to 62 $\times$ 1.04 $\approx$ 64 observations per arm. Given an anticipated drop-out rate at follow-up of 10%, 128/0.9 $\approx$ 144 patients should be randomised.

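### Worsening of symptoms is compared between arms only through adverse-event reports with no stated criterion, mostly from contacts with unblinded therapists, and the blinded HRSD-24 is not used to count patients who worsened

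*Protocol*

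**What the plan says.** **What counts as safety.** Protocol section 2: "Safety is assessed in terms of rates of AEs and SAEs". Section 10.5.9 turns this into tables by arm in the safety set: event numbers and incidences for main categories A to H, with a Wilson 95% interval per arm, for all AEs and for SAEs, split by onset during or after treatment. Table 3 names the risk difference as the summary measure for safety.

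**How worsening is defined.** Section 7.1 lists "A) Worsening of psychopathological symptoms" as the first of eight categories. It gives no scale, size of change or reference time. Section 7.2 grades severity only from mild to severe. The definitions are said to be based on a standardised questionnaire from earlier psychotherapy trials, whose content the protocol does not reproduce.

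**Who reports.** Section 7.2: "The documentation obligation of AEs applies to the study psychotherapist or rater who first became aware of the event". Section 5.3.1: "During group sessions, study psychotherapists will encourage patients to report any adverse events either during the session or confidentially"; the therapist then documents them. Section 3.4 says that "blinding of patients and study psychotherapists performing the interventions is not possible", and section 3.5.4 has every therapist run both kinds of group. Yet section 3.4 also says that "data acquisition other than patient reported outcomes will be done by trained blinded clinical raters not involved in patient management".

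**What the blinded scale is used for.** Blinded raters score the HRSD-24 at screening, W9 and W21 (Table 5, section 5.4.2). Its planned uses are mean relative change, response, remission and, in section 7.4, a cut-off on one suicidality item.

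**The concern.** The protocol has an objective to assess the safety of IPT-Work in comparison to SP. For worsening, that comparison depends on when a reporter decides that a patient is worse, and most opportunities to report fall to someone who knows the arm. With no criterion to hold the threshold constant, a difference in category A could come from the treatment or from the reporting, and the planned tables could not separate the two.

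A better-protected measure of the same thing is already collected in both arms. As planned, it shows only benefit. A difference in means and two responder-type rates do not reveal whether a subset of patients became worse.

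**Working it through.** **1. Contacts at which AEs are collected (Table 5).** V2 to V11 are treatment sessions, so 10 contacts. V12 and V13 are rater visits, so 2. The share with an unblinded therapist is 10/12 = 83%.

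**2. What differential reporting could do (assumed sensitivities).** The protocol gives no reporting sensitivity. Suppose 20% worsen in both arms, and 90% of cases are recorded in one arm against 50% in the other. The tables would show 0.20 × 0.90 = 18% against 0.20 × 0.50 = 10%, a false risk difference of 8 points. If the sensitivities are swapped, the sign reverses.

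**3. The planning inputs.** Section 10.4 assumes means that "differ by 28.0% points with a common SD of 55.0" per cent. A two-sided 5% t-test with 62 per arm has power 0.803, which reproduces the stated 80%. With 72 randomised per arm and 10% drop-out, 72 × 0.9 = 64.8, so about 65 per arm are observed at follow-up.

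**4. Did anyone worsen in the pilot?** Relative decrease cannot exceed 100%. For values with upper limit 100, variance ≤ (100 − mean) × (mean − minimum), so minimum ≤ mean − variance/(100 − mean). The pilot TAU figures are 22.6% ± 71.6%. Assuming 14 of the 28 patients per arm, the variance with divisor n is 71.6² × 13/14 = 4760. The minimum is then at most 22.6 − 4760/77.4 = −38.9. At least one TAU patient must have worsened by about 39%. With 10 or 18 patients in the arm, the figure is 37% or 40%.

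**5. Illustrative shares with any rise above baseline at follow-up.** Let R = post/pre, with mean 1 − (mean decrease)/100. The share is P(R > 1).
- Normal: Φ(−mean decrease/SD).
- Lognormal: s² = ln(1 + (SD/mean)²), μ = ln(mean) − s²/2, share Φ(μ/s).
- Gamma: shape (mean/SD)², scale SD²/mean.

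The SP mean is not in the protocol; it is assumed as 62.2 − 28.0 = 34.2.

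| Mean decrease ± SD | Normal | Lognormal | Gamma |
|---|---|---|---|
| IPT-Work 62.2 ± 28.0 (both pilot) | 1% | 4% | 4% |
| IPT-Work 62.2 ± 55.0 (pilot mean, planning SD) | 13% | 7% | 11% |
| SP 34.2 ± 55.0 (assumed mean, planning SD) | 27% | 17% | 21% |

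Of 65 observed patients, this is about 1 to 8 in IPT-Work and 11 to 17 in SP. The normal column is an approximation, because it ignores the upper limit of 100%.

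**6. Precision of the proposed table.** Wilson 95% intervals with 65 patients: 6/65 gives 4.3% to 18.7%, 13/65 gives 12.1% to 31.3%, 18/65 gives 18.3% to 39.6%. The table would be descriptive, as is all safety analysis in this trial.

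**The case against.** **Blinded raters also report.** They are trained in (S)AE assessment (section 3.4), AEs are collected at V12 and V13, and section 7.2 obliges a rater who first becomes aware of an event to document it. A patient found worse at W9 or W21 should therefore enter category A. This stands as a real mitigation. It does not supply a criterion, and it does not change who first hears of most events during treatment.

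**Reporting opportunity is symmetric.** Session number and duration are equal, and the same therapists run both arms. This also stands, but knowledge of the arm remains.

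**The questionnaire may contain a criterion.** It may. The point is limited to what the protocol states.

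**This is a matter for the SAP.** Section 10.5.1 already gives minimum, quartiles and maximum of scores by arm and time point, and allows continuous variables to be shown in categories, so an SAP could add such a table. But the protocol itself fixes safety as AE and SAE rates and sets out the tables, and a minimum shows one patient, not a rate.

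**The scale has gaps.** The HRSD-24 is not taken between V2 and V11, drop-outs have no score, rater blinding is kept only where possible (section 3.5.3), and small rises include rating noise. All true, which is why the table can only stand beside category A.

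**What a reader might wrongly infer.** One might conclude that worsening will be under-counted. The documents do not show this: without a threshold the error can go either way, and ten therapist contacts may catch transient worsening that two ratings miss. One might also call worsening the main harm, but section 7.1 does not rank its eight categories.

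**Conclusion.** The point holds in limited form. Worsening is compared between arms only through reports with no criterion stated in the protocol. Of the 12 AE contacts, 10 are with therapists who know the arm, so the comparison is open to reporter bias of unknown direction and size. The blinded HRSD-24 at W9 and W21 is not used to count patients who worsened.

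The percentages above are illustrations, not estimates. The IPT-Work figure depends on whether the pilot SD of 28.0 or the planning SD of 55.0 is used, the SP mean is assumed, and any rise is counted, however small. They do not establish that deterioration will be common. The contrast between 13% and 27% arises only from shifting the mean at equal SD, so it restates the assumed efficacy difference and is no separate harm signal. What does not depend on the shape of the distribution is that the pilot TAU figures require at least one substantial worsening, given an assumed arm size.

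Separately, section 3.4 on blinded data acquisition contradicts sections 5.3.1 and 7.2 on therapists documenting AEs.

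**What to change.** In section 10.5.9, add one descriptive table by arm of HRSD-24 deterioration at W9 and at W21:
- number and percentage of patients with a score above baseline, and with a larger rise whose size is fixed before database lock;
- 95% confidence intervals, and the between-arm risk difference that Table 3 already names for safety;
- number of patients with a missing score at each visit;
- number of worsened patients with and without a category A report.

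State that the table supplements category A, because small rises include rating noise, drop-outs have no score and worsening between visits is not captured.

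Reconcile section 3.4 with sections 5.3.1 and 7.2, so that the protocol says consistently who acquires AE data and whether that person knows the arm.

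The cost is one table from data already collected and a few sentences in the protocol or SAP. Sample size, visits and clinical procedures do not change.
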